## Abstract

**Objective::**

The therapeutic landscape for localized prostate cancer (PC) is evolving. Stereotactic radiotherapy (SRT) has been reported to be at least not inferior to standard radiotherapy, but the effect of androgen deprivation therapy (ADT) in this setting is still unknown and its use is left to clinical judgment. There is therefore the need to clarify the role of ADT in association with SRT, which is the aim of the present study.

**Methods::**

We present a study protocol for a randomized, multi-institutional, Phase III clinical trial, designed to study SRT in unfavorable intermediate and a subclass of high-risk localized PC. Patients (pts) will be randomized 1:1 to SRT + ADT or SRT alone. SRT will consists in 36.25 Gy in 5 fractions, ADT will be a single administration of Triptorelin 22.5 mg concurrent to SRT. Primary end point will be biochemical disease-free survival. Secondary end points will be disease-free survival, freedom from local recurrence, freedom from regional recurrence, freedom from distant metastasis and overall survival (OS); quality of life QoL and patient reported outcomes will be an exploratory end point and will be scored with EPIC-26, EORTC PR 25, IPSS, IIEF questionnaires in SRT + ADT and SRT alone arms. Moreover, clinician reported acute and late toxicity, assessed with CTCAE v. 5.0 scales will be safety end points.

**Results::**

Sample size is estimated of 310 pts. For acute toxicity and quality of life results are awaited after 6 months since last patient in, whereas, for efficacy end points and late toxicity mature results will be available 3–5 years after last patient in.

**Conclusion::**

Evidence is insufficient to guide decision making concerning ADT administration in the new scenario of prostate ultra-hypofractionation. Hence, the need to investigate the ADT role in SRT specific setting.

**Advances in knowledge::**

The stereotactic prostate radiotherapy with or without ADT trial (SPA Trial) has been designed to establish a new standard of care for SRT in localized unfavorable intermediate and a subclass of localized high risk PC.

## Introduction

### Background

Radiotherapy (RT) for the treatment of localized prostate cancer (PC) is changing. The ProtecT trial showed no differences in terms of overall survival (OS) and progression-free survival (PFS) for patients treated with RT *vs* radical prostatectomy *vs* active monitoring, with a different toxicity profile among the three options.^
1
^ The observation of a lower than expected α/β ratio in PC cells has led to explore moderate hypofractionation schedules, that are actually considered not inferior to the normofractionated radiation regimes, thanks to the results of the CHHiP, the PROFIT, and the RTOG 0415 trials. Brachytherapy boost plus normofractionated external beam radiotherapy (EBRT) is also an option in this setting of patients.^
2–4
^

The dramatic technical innovation in recent years allowed to explore feasibility and safety of stereotactic body ablative radiotherapy (SRT) schedules in PC. SRT has the advantage to deliver high-precision, high-dose RT in a short period of time (generally 1 to 8–10 fraction), with a convenience for patients and RT facilities. A broad spectrum of Phase I, II and III clinical trials and a recent meta-analysis showed promising results in terms of local control, biochemical relapse-free survival and relapse-free survival with an acceptable risk for toxicity using a 7-fractions schedule, mainly genitourinary (GU) side-effects. Remarkably the 5-fraction SRT schedule was associated with a slightly worse acute GU toxicity profile and an equal late GU toxicity risk profile in comparison to standard EBRT.^
5–7
^

The PACE-B non-inferiority, randomized, Phase III trial, comparing the efficacy of 5-fraction SRT schedule with moderately hypofractionated RT for the treatment of low and intermediate risk PC patients in terms of freedom from biochemical recurrence and disease-free survival (DFS) is also ongoing.

Results of HYPO-RT-PC Phase III randomized trial have been recently published, with intermediate and high risk PC patients in SRT arm presenting non-inferior outcomes compared to normofractionation. Androgen deprivation therapy (ADT) was not permitted in both trials, either in the standard arm nor in the experimental one.^
6
^

### Unfavorable intermediate and high-risk prostate cancer: SRT–ADT dilemma

D’Amico/NCCN risk stratification of disease is an essential strong prognostic factor in PC. Intermediate risk class has been further divided in two subgroups with different prognosis, favorable intermediate and unfavorable intermediate risk. In case of normofractionated and moderate hypofractionated schedules there is evidence that short-term ADT combined with RT improves OS, PFS and biochemical disease-free survival (bDFS). Despite these results, the attitude of clinicians has been slightly different for prostate SRT, with the frequent omission of ADT in the absence of clear and consolidated data in literature; with no clinical trials ongoing to clarify this issue. Such clinical attitude may be motivated by the possible better local control that ablative SRT can guarantee. Nevertheless, emerging evidence from large cohorts studies has shown that unfavorable intermediate risk PC patients treated with SRT present a bDFS not so different from high risk patients. Katz et al published a series of 515 patients undergoing SRT for localized PC. The 47 unfavorable intermediate risk patients presented outcomes quite similar to the high-risk cohort, with a 7 year bDFS of 68 and 65%, respectively. Pattern of relapse was equally distributed among local, distant and biochemical ones, the latter probably reflecting micro-metastatic disease not detectable with current imaging techniques such as Fluoro-Choline positron emission tomography (PET) CT, bone scan and contrast enhanced CT.^
8
^ The authors conclude that ADT may be of limited benefit in this scenario but given the relatively high rate of relapses in unfavorable intermediate cohort, novel strategies to improve DFS are warranted.

Evidence of the benefit of adding ADT to normofractionated and moderately hypofractionated EBRT for high risk PC patients is even stronger. Despite this, translating the evidence deriving from these studies to ultra-hypofractionation could be tricky, given the different response to high dose per fraction of PC cells.^
8,9
^ Conversely, the attitude of omitting concurrent ADT in the context of prostate SRT has been clear in recent literature.

Remarkably, in 2016, the randomized Phase III study from Bolla and colleagues demonstrated that combining short-course ADT with normofractionated EBRT improves 5 year bDFS and DFS over RT alone for intermediate and high risk PC patients (hazard ratio 0.52 and 0.63, respectively). Interestingly, there was a statistically significant reduction in 5 year local relapses rate from 6 to 2%, and in the distant metastasis rate from 7.6 to 4.4% (hazard ratio 0.37 in both cases) in the combination arm.^
10
^

Another reason which may explain the frequent omission of short-term ADT in unfavorable intermediate risk patients eligible for SRT could be related to concerns about the ADT side-effects. Also, in the context of SRT prospective studies identified an increased risk of acute and late GU toxicity in SRT + ADT arm, with a mechanism not completely clear.^
11
^ Interestingly, Bolla and colleagues in the former randomized, Phase III trial also performed a QoL analysis with HRQOL questionnaires (EORTC QoL questionnaires C30 supplemented with a QLQ-PR25) and showed no clinically relevant differences in HRQOL scores between the groups. As experienced ADT-related symptoms, as well, were more clinically evident and significantly worse in the ADT arm, at month 6 and at year 1, as sexual activity and functioning scales. However, no marked difference was seen between the arms from year 2 onward. Nevertheless, this trial did not consider the impact of ADT on endocrine homeostasis, as reported in a wide body of literature.^
12–14
^

### Rationale for study design and hypothesis

The present study aims to clarify the role of short-term ADT in the context of unfavorable intermediate and a subclass of high risk PC patients eligible for prostate SRT. Prostate SRT has been endorsed as an option for primary radical treatment of PC. The benefit of ADT is still unknown and previous evidence are insufficient in this setting of patients and the final clinical decision is left to clinical judgement.

### Objective of the trial

For the reasons discussed, it seems to be relevant to propose a randomized, open label, Phase III clinical trial to compare prostate SRT plus 6 months ADT *vs* prostate SRT alone for the treatment of unfavorable intermediate and a subgroup of high risk PC patients, with the aim of demonstrating if SRT + ADT is superior to SRT alone.

### Endpoints of the study

#### Primary end point

Primary end point will be to determine if there is any improvement in bDFS, defined as prostate-specific antigen (PSA) rising ≥2 ng ml^−1^ over PSA Nadir, following the Phoenix criteria for biochemical recurrence of PC (after primary RT) in patients treated with prostate SRT plus ADT (ARM A) compared to patients treated with SRT alone (ARM B).

Study end points are summarized in Table 1.

**Table 1. T1:** Study end points

PRIMARY END POINTS	SECONDARY END POINTS
Determine if there is any improvement in bDFS in patients treated with prostate SRT plus ADT (ARM A) compared to patients treated with SRT alone (ARM B)	DFS FFLR FFRR FFDM OS

bDFS, biochemical disease-free survival; FFDM, freedom from distant metastasis; FFLR, freedom from local recurrence; FFRR, freedom from regional recurrence; OS, overall survival.

All biochemical failures need to be confirmed with a second PSA detection meeting the criteria for failure. In addition, it is now recognized that a benign PSA bounce may be seen in up to 20% of patients after SRT, usually within the first 2 years.^
15
^

In some cases, the magnitude of the PSA bounce may be considered as high enough for the patient to be incorrectly classified as a PSA failure. To prevent this, for patients receiving SRT, PSA failure before 24 months after the treatment will require three consecutive PSA rises to resulting a clinical diagnosis of failure, or the start of further treatment (androgen deprivation therapy). Over 24 months, the definition of PSA failure for SRT will refer to the Phoenix definition described above (*i.e.* PSA nadir+2 ng ml^−1^).

QoL and patient reported outcomes (PROs) will be an exploratory end point and will be scored with questionnaires EPIC-26, EORTC PR 25, IPSS, IIEF in SRT + ADT and SRT alone arms.

Moreover, Clinician reported Acute Toxicity, assessed with CTCAE v. 5.0 scales and Clinician reported Late Toxicity, assessed with CTCAE v. 5.0 scales will be safety end points.

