## Methods and materials

### Trial design and allocation ratio

This is a multicenter, open label, randomized-controlled, Phase III study. Randomization will be 1:1 and will be accounted for minimization with a balancing algorithm for two variables:patients age <70 vs ≥70unfavorable intermediate risk and a subgroup of PC high risk group

In arm A, patients will be treated with prostate SRT to a total dose of 36.25 Gy in 5 fractions (consecutive or alternate days) plus 6 months of ADT consisting in LHRH analog (Triptorelin 22.5 mg). In arm B, patients will be treated with prostate SRT alone to a total dose of 36.25 Gy in 5 fractions (consecutive or alternate days) (Figure 1).

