**Figure 2. F2:**
[figure not shown]
Pre-randomization and follow-up assessment of PSA, testosterone, toxicity, PRO e QoL questionnaires in details. PRO, patient reported outcome; PSA, prostate-specific antigen; QoL, quality of life.

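### The rule for PSA failure before 24 months does not say that nadir + 2 still applies or whether starting ADT alone is an event, so the primary end point can misclassify men differently in the two arms

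*Protocol article*

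**What the plan says.** The Primary end point section of the protocol article builds the definition in steps.

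- Headline definition, the Phoenix criterion, with the rise measured from the nadir: "Primary end point will be to determine if there is any improvement in bDFS, defined as prostate-specific antigen (PSA) rising ≥2 ng ml^−1^ over PSA".
- Confirmation: "All biochemical failures need to be confirmed with a second PSA detection meeting the criteria for failure".
- Reason for a special early rule: "a benign PSA bounce may be seen in up to 20% of patients after SRT, usually within the first 2 years". The text adds that some bounces are large enough to be mistaken for failure.
- Early rule: "PSA failure before 24 months after the treatment will require three consecutive PSA rises to resulting a clinical diagnosis of failure", followed by "or the start of further treatment (androgen deprivation therapy").
- Late rule: "Over 24 months, the definition of PSA failure for SRT will refer to the Phoenix definition described above".

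Three facts from other sections matter. Under Trial design and allocation ratio: "This is a multicenter, open label, randomized-controlled, Phase III study", and only Arm A receives the LHRH analogue, for 6 months. Under Outcome measures and study timeline, ADT is given between 12 weeks before radiotherapy and immediately before it, and visits are every 3 months in year 1, every 4 months in year 2 and every 6 months after that. The caption of Figure 2 reads "Pre-randomization and follow-up assessment of PSA, testosterone, toxicity, PRO e QoL questionnaires in details", so testosterone is among the items assessed, but the figure itself cannot be seen here. No sentence in the end point section uses testosterone.

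**The concern.** The early rule exists to make a false call of failure less likely. Taken at its word, it can do the reverse. It names a number of rises but no size, and the next sentence gives the nadir + 2 threshold to the later period. A man whose PSA climbs in three small steps from a very low nadir would meet it without coming near nadir + 2.

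That pattern is to be expected in one arm in particular. Arm A men come off a 6-month LHRH analogue during the early window, and PSA can rise as testosterone returns without any recurrence. False failures there would hide a real benefit of ADT.

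The second limb, starting ADT, carries no PSA criterion. If it stands alone as an event, it depends on the judgement of a clinician who knows the allocation. It also fits badly with the sentence requiring a second qualifying PSA for every biochemical failure. Extra events of this kind in Arm B, whose men have had no trial ADT, would create an apparent benefit.

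**Working it through.** **1. The text.** Two questions have no clear answer in the article. (a) Before 24 months, do three rises replace nadir + 2 or come on top of it? The headline definition and the anti-bounce purpose point to an addition; the split at 24 months points to a replacement. (b) Is an ADT start an event in itself, or only the consequence of three rises? The sentence allows both.

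**2. Timing.** A 6-month course started between 12 weeks before radiotherapy and the day before it ends about 3 to 6 months after radiotherapy. Visits before 24 months fall at 3, 6, 9, 12, 16 and 20 months. PSA is named explicitly only at 3 months; I assume it is taken at each visit. There is then room for three consecutive rises after drug cover ends and inside the early window. A second PSA does not prevent this, since a continuing recovery rise meets the same criterion again.

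**3. The plan's own power.** Inputs from Sample size determination: 155 per arm, 5-year bDFS 95% (A) and 85% (B), two-sided α 0.05. With failure proportions pA = 0.05, pB = 0.15 and mean p = 0.10:

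- SE0 = √(2 × 0.10 × 0.90 / 155) = 0.03408
- SE1 = √((0.05 × 0.95 + 0.15 × 0.85) / 155) = 0.03360
- Power = Φ((0.10 − 1.96 × 0.03408) / 0.03360) = Φ(0.988) = 83.85%

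This reproduces the stated 83.9%. Expected failures are 155 × 0.05 = 7.75 and 155 × 0.15 = 23.25, 31 in all, so a handful of misclassified men matters.

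**4. False failures in Arm A (assumed rate f among men otherwise event-free).** pA = 0.05 + 0.95f, pB = 0.15, same formula.

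| f | Extra Arm A events | pA | Power |
|---|---|---|---|
| 1% | 1.5 | 0.0595 | 74% |
| 2% | 2.9 | 0.0690 | 63% |
| 3% | 4.4 | 0.0785 | 51% |
| 5% | 7.4 | 0.0975 | 29% |

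**5. Extra ADT-start events in Arm B with no true effect (assumed rate g).** pA = 0.15, pB = 0.15 + 0.85g. The chance of a significant result favouring ADT is nominally 2.5%.

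| g | Extra Arm B events | pB | Chance of a false win for ADT |
|---|---|---|---|
| 1% | 1.3 | 0.1585 | 4.0% |
| 2% | 2.6 | 0.1670 | 6% |
| 3% | 4.0 | 0.1755 | 9% |
| 5% | 6.6 | 0.1925 | 17% |

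Exact binomial calculation gives 8.9% and 16.9% in the last two rows; the normal approximation gives 8.8% and 16.6%.

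**6. Can a recovery rise meet the literal rule?** This is an illustration with an assumed course. PSA rises in a straight line from 0.05 to 0.30 ng/ml starting at month 6, with 10–20% measurement noise, at the six visits above. If the rise lasts to month 20, 88–99.7% of simulated courses contain three consecutive rises. If it levels off at month 12 the figure is 72–75%, and at month 9 about 33%. No simulated value exceeds 1 ng/ml, so none reaches nadir + 2. The result depends heavily on the assumed shape, and confirmation by a further rise would lower it.

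**The case against.** The strongest reply is that nadir + 2 was never meant to be dropped. The section opens with it. The early rule is introduced because a bounce may be large enough to be wrongly called a failure, and its verb is one of requirement. A looser criterion would defeat that purpose, and a rule that failed most recovering men could not coexist with the 95% bDFS planned for Arm A. Likewise, the ADT limb can be read as three rises that lead either to a clinical diagnosis or to treatment. On that parse it is no separate trigger and there is no conflict with the confirmation sentence. The early rule also mentions a clinical diagnosis, which the simulation above ignores.

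Much of this stands. It shows that the literal reading is probably not what was intended. It does not show that the text says what was intended: the contrast with the period after 24 months remains, and two centres could classify the same man differently. It is also fair that a condensed article may leave testosterone handling, adjudication and sensitivity analyses to the full protocol or the SAP, so their absence is not the point here.

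A reader might go further and infer that Arm A men will be falsely failed, that clinicians will start ADT selectively in Arm B, or that the sentences flatly contradict each other. The documents do not support that. They give no recovery course, no false-failure rate and no rate of early ADT starts. Open-label discretion exists in both arms, and the contradiction arises on only one parse.

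**Conclusion.** The concern holds as a defect in how the primary end point is fixed. As written, the early rule permits an event without the size threshold that defines bDFS and, on one parse, an event with no PSA criterion at all. Either can act differently by arm.

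The size is conditional. With about 31 expected events, assumed misclassification of 3–5% in Arm A lowers power to about 51–29%. With no true effect, 3–5% extra events in Arm B raise the chance of a false win for ADT to about 9–17%. These rates are mine, not the trial's. The two biases run in opposite directions and the net direction is unknown, but one cannot be relied on to cancel the other. The sample-size arithmetic itself is sound.

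**What to change.** Reconcile the sentences in one endpoint paragraph that applies to both arms and to outcome classification only:

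- Before 24 months, three consecutive rises are required in addition to a confirmed PSA of at least nadir + 2, not in place of it.
- An ADT start counts in the primary analysis only when confirmed PSA failure or recurrence is documented.
- Sensitivity analyses: one counting every ADT start and, where testosterone was measured, one excluding rises that accompany testosterone recovery.

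The cost is an amendment of one paragraph, best made before outcomes are reviewed by arm. The downside is small: some true early failures may be dated a visit or more later, not necessarily equally in the two arms. The change concerns how outcomes are classified, not when or how patients are treated.

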## Methods and materials

### Trial design and allocation ratio

This is a multicenter, open label, randomized-controlled, Phase III study. Randomization will be 1:1 and will be accounted for minimization with a balancing algorithm for two variables:patients age <70 vs ≥70unfavorable intermediate risk and a subgroup of PC high risk group

In arm A, patients will be treated with prostate SRT to a total dose of 36.25 Gy in 5 fractions (consecutive or alternate days) plus 6 months of ADT consisting in LHRH analog (Triptorelin 22.5 mg). In arm B, patients will be treated with prostate SRT alone to a total dose of 36.25 Gy in 5 fractions (consecutive or alternate days) (Figure 1).

**Figure 1. F1:**
[figure not shown]
Patient pathway in SPA trial protocol.

### Key inclusion criteria

Age 18–80 years old.Histological confirmation of prostate acinar adenocarcinoma with a minimum of 10 biopsy cores taken by prostate biopsyProstate protocol MRI for local stagingPatients belonging to unfavorable intermediate group according to the D’Amico/NCCN risk group classificationPatients belonging to a subclass of high-risk group according to the D’Amico/NCCN risk group classification:

ISUP Group 4 (GS 4 + 4, 3 + 5, 5 + 3), orcT3a stage, orPSA>20

Eastern Cooperative Oncology Group (ECOG) PS 0–2IPSS 0-15Prostate volume less than 100 ccNo pathologic lymph nodes and distant metastasis on PET scan or CT scan plus bone scan

Details about inclusion and exclusion criteria are fully reported in Table 2 and study protocol.

**Table 2. T2:** Study inclusion criteria

KEY INCLUSION CRITERIA	
Age 18–80 years old ECOG PS 0–2 Histological confirmation of prostate acinar adenocarcinoma with a minimum of 10 biopsy cores taken by prostate biopsy Patients belonging to unfavorable intermediate group according to the D’Amico/NCCN risk group classification: Grade Group 3 or/and 2–3 risk factors for intermediate category (PSA 10–20/Grade Group 2–3/cT2a cT2b) or/and Biopsy cores positive ≥50% Patients belonging to a subclass of high-risk group according to the D’Amico/NCCN risk group classification: ISUP Group 4 (GS 4 + 4, 3 + 5, 5 + 3) or cT3a stage or PSA >20	Prostate protocol MRI for local staging Prostate volume less than 100 cc No pathologic lymph nodes and distant metastasis on PET scan or CT scan plus bone scan PSA detection maximum 60 days before randomization IPSS 0–15 Ability of the patient to understand and sign a written informed consent document Ability and willingness to comply with patients reported outcome questionnaires schedule during the study time Contraceptive measures for patients with partners with reproductive potential must be explained

ECOG, Eastern Cooperative Oncology Group; PET, positron emission tomography; PSA, prostate-specific antigen.

### Interventions

### Arm A

Patients in ARM A will be treated with SRT on the prostate (consecutive days or at alternate days to a total dose of 36.25 Gy administered in 5 fractions (7.25 Gy/fraction) plus LHRH analog (Triptorelin 22.5 mg), one administration before SRT. An anti-androgen drug (es. Bicalutamide 50 mg) must be administered daily starting from 7 days before LHRH analog administration to 10 days after to prevent the flare effect.

